|                                                                          | Each item is scored on a 7-point Likert scale ranging from 1-7.

Items are summed to create one score for each domain.                                                                     |                                                                                                                                                                                                                                                                             |                           |                                                                                                                                                |
| Number and severity of leakage episodes                                  | Collected by the participant in a custom-developed 7-day Accident Diary.                                                                                                                         | Whole numbers/ counts from 0 overall and within categories of damp, wet and soaked. Reported as mean (SD) or median (IQR).                                                                                                                                                  | Baseline, 17 and 52 weeks | Poisson regression using generalised estimating equations to account for clustering, adjusting for stratification factor and physiotherapist.  |
| Number of leakage episodes by provocation                                | Collected by the participant in a custom-developed 7-day Accident Diary.                                                                                                                         | Whole numbers/counts from 0 within seven categories of provocation: i) urgency urinary incontinence, ii) stress urinary incontinence, iii) mixed urinary incontinence, iv) post-micturition leakage, v) nocturnal enuresis, vi) postural urinary incontinence, vii) unknown | Baseline, 17 and 52 weeks | Poisson regression using generalised estimating equations to account for clustering, adjusting for stratification factor and physiotherapist.  |

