| Number of continence pads used                                           | Collected by the participant in a custom-developed 7-day Accident Diary.                                                                                                                         | Whole numbers/ counts from 0. Reported as mean (SD) or median (IQR).                                                                                                                                                                                                        | Baseline, 17 and 52 weeks | Poisson regression using generalised estimating equations to account for clustering, adjusting for stratification factor and physiotherapist.  |
| Patient Global Impression of Change (PGIC) Global Rating of Change Scale | Self-reported in response to “Compared to your first assessment in this study (when you completed your baseline information 17 weeks ago) overall, how would you rate your bladder control now?” | Participants indicating they are “much improved” or “very much improved” will be classified as improved. All other respondents will be classified as not improved.                                                                                                          | 17 and 52 weeks           | Logistic regression using generalised estimating equations to account for clustering, adjusting for stratification factor and physiotherapist. |

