|                                                                                               | Responses will be captured on a on a 7-point Likert scale ranging from 1=very much worse to 7= very much improved                                                                                                                                                                                                                                                                                                                                                                                                                                                                                     |                                                                                                                                             |                           |                                                                                                                                                                                                                                                                                                                             |
| International Physical Activity Questionnaire Short last 7 days Self-Administered Format [48] | 
A 4-item self-reported questionnaire capturing time spent (days, hours, minutes) on vigorous physical activities, moderate activities, walking and sitting in the past 7 days.
 
Responses can be converted into categorical and/or continuous scores.
 
Categorical: converted into two physical activity categories
Category 1: Low / inactive
Category 2: Moderate or High
 
Continuous: reported as median METminutes for walking (W), moderate-intensity activities (M), and vigorous-intensity activities (V) (METs are multiples of the resting metabolic rate).
 | 
Categorical: reported as number and %
 
Or
 
Continuous: counts from 0 reported as median values and interquartile ranges.
 | Baseline, 17 and 52 weeks | 
Constrained longitudinal data analysis across all time points (continuous outcome), accounting for stratification factor and physiotherapist.
 
Logistic regression (binary outcome) using generalised estimating equations to account for clustering, adjusting for stratification factor and physiotherapist.
 |

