## 12. STATISTICAL METHODS

### 12.1 Sample Size Estimation

We aim to detect a minimal clinically important difference (MCID) of 2.5 units [35] over 17 weeks in the primary outcome of change in urinary incontinence measured using the ICIQ-UI SF[34]. The sample size calculation accounts for potential clustering by physiotherapists in the intervention arm. Based on previous research[35], we assume a conservative between-participant standard deviation of 3.2 units. We have also assumed a conservative correlation between baseline and 17-week scores of 0.4, an intra-cluster correlation of 0.05 and 3 physiotherapists treating approximately 10 patients each. With these parameters, we need 30 women per arm to achieve 80% power to detect the MCID at a 0.05 significance level. Allowing for 15% attrition, we will recruit 36 women per arm (in total n=72).

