### 12.2 Statistical Analysis Plan

All analyses will be described *a priori* in a detailed Statistical Analysis Plan and published while biostatisticians are blinded to treatment allocation. Demographic and baseline characteristics of participants will be summarised as appropriate (means and standard deviations for continuous variables that appear to be distributed approximately symmetrically, medians and interquartile ranges for other continuous variables, counts and percentages for categorical variables). Main comparative analyses between groups will be performed using intention-to-treat. Constrained longitudinal data analysis will be used to analyse continuous outcomes, including the primary outcome. The response will consist of all continuous outcomes (baseline, 17 weeks and 52 weeks) and the model will include factors representing treatment group, time (categorical), and a group-by-time interaction, with the restriction of a common baseline mean across treatment groups. Models will include the stratification

variable (radiotherapy) and random effects for physiotherapist (intervention arm only). The mean change in urinary incontinence (primary outcome) and other continuous outcomes (ICIQ-LUTSqol, PFBQ, EQ-5D-5L, UTAUT-II domains 1-9, METminutes (walking, moderate-intensity activities, vigorous-intensity activities) from baseline to each follow-up time-point between the two intervention groups will be obtained. The primary hypothesis will be evaluated by obtaining the estimated differences between the two intervention arms in mean change in urinary incontinence score from baseline to 17-weeks post-commencement of treatment (primary time point), two-sided 95% confidence intervals and p-values. These models provide valid inference in the presence of missing data if the data are missing at random. Standard diagnostic plots will be used to check model assumptions. Treatment effects at 52 weeks post-randomisation (secondary time point) will be estimated to assess maintenance of treatment effects for all outcomes except UTAUT-II domains 1-9 for which only 17-week follow-up data will be collected.

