The binary secondary outcomes (PGIC and physical activity category) will be compared between groups separately using logistic regression, adjusting for the stratifying variable of radiotherapy, and fit using generalized estimating equations to account for clustering, with results reported as risk ratios and risk differences. Poisson regression models fitted using generalized estimating equations will be used for secondary count outcomes (number of leakage episodes overall and by severity and provocation, number of continence pads used).

The economic evaluation will have a societal perspective and will assess both the cost of the intervention at 17 weeks and the cost-effectiveness and cost-utility of the intervention group *versus* the control group at 52-weeks. Quality-adjusted life years (QALYs) gained [56] for the intervention compared to control at 52 weeks will be assessed. QALYs will be calculated based on utility scores using the EQ-5D-5L [44, 45] at baseline and 52 weeks. QALYs will also be calculated using the ICIQ-LUTSqol [42], a condition specific quality of life measure, at baseline and 52 weeks. Analysis will be combined with the primary clinical outcome measure to establish the incremental cost-effectiveness ratio of the intervention. The difference in participant resource use related to incontinence (e.g. pad use, medication use, health service use) and productivity lost between baseline and 52 weeks will be compared for intervention and control groups. The association between utility gains on the EQ-5D-5L and productivity will be compared between the intervention and control groups. The 52-week economic evaluation will be reported separate from the main trial.

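### The count and activity-category models list no adjustment for the baseline value already collected for each outcome, which costs precision and leaves them exposed to arm-specific dropout

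*Protocol*

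**What the plan says.** The section 4.6 table gives the same model for leakage number and severity, leakage by provocation, and pads: "Poisson regression using generalised estimating equations to account for clustering, adjusting for stratification factor and physiotherapist". For the binary form of the physical activity questionnaire it gives "Logistic regression (binary outcome) using generalised estimating equations to account for clustering, adjusting for stratification factor and physiotherapist". The time-points column for all of these rows reads "Baseline, 17 and 52 weeks".

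Section 12.2 is shorter. For counts it states only that "Poisson regression models fitted using generalized estimating equations will be used for secondary count outcomes" and names no covariate. For the binary outcomes it has "adjusting for the stratifying variable of radiotherapy, and fit using generalized estimating equations to account for clustering". The synopsis agrees with section 12.2.

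The continuous outcomes are handled differently. Their rows specify a constrained longitudinal analysis over all time points, and section 12.2 puts baseline in the response vector "with the restriction of a common baseline mean across treatment groups".

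**The concern.** The protocol uses baseline information for the continuous outcomes and lists none for the counts and the activity category, although the data are collected. The activity row shows both treatments in one cell: the continuous score is analysed over all time points, while the binary version of the same questionnaire has two adjusters and no mention of baseline.

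Baseline matters here for two reasons. Eligibility in section 5.2.1 sets a floor on leakage frequency but no ceiling, so weekly counts may differ widely between women. Randomisation in section 5.4 is stratified by radiotherapy alone, so with 36 women per arm nothing in the design or the listed models limits a chance difference in starting severity.

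At stake are the precision of the diary and activity comparisons and their robustness to missing data. Section 12.1 allows for 15% attrition. The telephone fallback in section 5.6 covers only the primary outcome measure, and the diary is a separate seven-day form, so diary data may be lost more often than the primary outcome.

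**Working it through.** **1. The protocol's own figure.** Section 12.1 states 30 women per arm for the primary outcome and no figure for the secondary outcomes. Its inputs are: difference 2.5 ("We aim to detect a minimal clinically important difference (MCID) of 2.5 units"), SD 3.2, baseline to 17-week correlation 0.4, intra-cluster correlation 0.05, about 10 patients per physiotherapist, 80% power and alpha 0.05 (two-sided, from section 12.2).

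- Unadjusted: n = 2 × [3.2 × (1.960 + 0.842) / 2.5]² = 25.7 per arm.
- Baseline adjustment: 1 − 0.4² = 0.84, giving 21.6.
- Design effect: 1 + (10 − 1) × 0.05 = 1.45. In both arms this gives 21.6 × 1.45 = 31.3. In the intervention arm only, the average is (1 + 1.45)/2 = 1.225, giving 26.5.
- Attrition: 30/0.85 = 35.3, rounded up to 36.

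The stated 30 lies between 26.5 and 31.3. Omitting the baseline factor with the one-arm design effect gives 31.5, which is also close, so the total does not prove how the correlation was used. It is, however, listed as an input: the protocol treats baseline as informative for the primary outcome.

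**2. Precision, linear approximation.** Adding baseline multiplies the variance of the treatment effect by 1 − r². Any r for these outcomes is an assumption.

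| r | variance factor | CI width factor | unadjusted n per arm matching 30 adjusted |
|---|---|---|---|
| 0.2 | 0.96 | 0.98 | 31.2 |
| 0.4 | 0.84 | 0.92 | 35.7 |
| 0.6 | 0.64 | 0.80 | 46.9 |
| 0.8 | 0.36 | 0.60 | 83.3 |

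**3. Precision, count model.** Poisson regression with robust variance was simulated with and without log(baseline count + 1): 30 women per arm, 1,500 replicates. The assumed inputs were a mean of 10 episodes per week, log-scale SD 0.8 and a true rate ratio of 0.70/0.95 = 0.737. Physiotherapist clustering was not simulated.

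| latent correlation | variance ratio, with / without baseline | variance removed |
|---|---|---|
| 0.4 | 0.91 | 9% |
| 0.6 | 0.80 | 20% |
| 0.8 | 0.55 | 45% |

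The correlation here is on the latent log scale, before Poisson noise, so it is not the same quantity as r in step 2. The gains are smaller than the linear formula suggests: worth about 1/0.91 = 1.10 and 1/0.80 = 1.25 times the sample at 0.4 and 0.6, against 1.19 and 1.56.

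**4. Dropout.** If dropout depends on baseline count in the same way in both arms and the rate ratio is constant, the women who remain have the same baseline mix in each arm and the unadjusted rate ratio is not biased. Bias needs a relation that differs by arm. The assumed example dropped 30% of intervention women above the median baseline count and 30% of control women at or below it, about 15% overall. True rate ratio 0.737:

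| latent correlation | without baseline | with baseline |
|---|---|---|
| 0.4 | 0.67 | 0.72 |
| 0.6 | 0.65 | 0.73 |
| 0.8 | 0.63 | 0.74 |

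The pattern is deliberately adverse. It shows that the mechanism exists, not how large the bias will be in this trial.

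**The case against.** The strongest reply is that covariates for secondary models are normally settled in the statistical analysis plan, to which section 12.2 defers, and that the section 12.2 sentence on counts names no covariate at all. That sentence alone would not support the point. The section 4.6 table does, because it states an adjustment set, and an analysis plan written to that set would leave baseline out.

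A second reply is that clustering is not defined for these models. Since physiotherapist is listed separately as an adjuster, the clustering could mean repeated measurements within a woman, with baseline as one of the responses. That reading is possible and cannot be excluded. It is not stated, whereas the continuous rows do state that all time points are used.

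Three stronger readings are tempting and should be set aside.

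- A reader might infer that the listed models give biased effects. With complete data, randomisation keeps them unbiased and the confidence interval allows for chance imbalance. Only the part of an imbalance that correlates with follow-up reaches the estimate.
- A reader might infer that the protocol wrongly claims missing-at-random validity for the GEE analyses. The sentence "These models provide valid inference in the presence of missing data if the data are missing at random" follows the constrained longitudinal models and precedes the GEE paragraph, so it makes no such claim for GEE.
- A reader might carry the 16% to 36% over to the counts and the activity category as they stand. Those figures come from a linear formula, and the 0.4 is the protocol's value for the ICIQ-UI SF. For a logistic model the formula does not apply directly, because adding baseline also changes the conditional odds ratio.

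It also stands that the reach is limited. Only secondary outcomes are involved, and physical activity is additionally analysed as a continuous score that does use baseline.

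**Conclusion.** The point holds as a matter of efficiency and robustness for secondary outcomes. As written, the models for leakage, pads and activity category omit a baseline value that the trial already collects. For the counts, the likely cost at a correlation of 0.4 to 0.6 is about 9% to 20% of the variance on the simulated model and 16% to 36% on the linear approximation. The gain for activity category has not been quantified. All of these figures rest on assumed correlations, and the simulation also on an assumed mean and dispersion.

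The exposure to dropout bias is conditional on dropout relating to baseline severity differently by arm, and nothing in the protocol says that it will. The change is worth making because it is free, but the trial's main conclusion does not depend on it: the primary analysis already uses baseline.

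**What to change.** In the section 4.6 table and in section 12.2, before unblinding:

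- Add the baseline value of the same outcome as a covariate: for example log(baseline count + 1) for the counts, and baseline category for activity. Where severity or provocation categories are sparse, as is likely with seven provocation categories in 72 women, use the overall baseline leakage count instead.
- State that the planned risk ratios and risk differences for activity category come from the adjusted logistic model by marginal standardisation. Under a constant rate ratio, the log-link count models need no such step.
- State the missing-data assumption for the GEE analyses.
- If the intention is for baseline to enter the GEE as a repeated response, say that instead, as the continuous rows do, and define the clustering unit.

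Adjusting PGIC, which has no baseline of its own, for baseline ICIQ-UI SF is optional. The cost is a clause in each place and one extra model term. No new data are needed and the sample size does not change.

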#### 3.2 Secondary Objectives

1. Aim: to investigate differences in quality of life (QoL) and condition-specific health-related QoL, bother of pelvic floor symptoms, leakage episodes, use of continence pads, global impression of change and the proportion that met or exceeded MCIDs for the primary outcome [35] (secondary outcomes) between the telehealth-delivered pelvic floor muscle training program incorporating a novel biofeedback device and usual care.
2. Aim: to evaluate processes within this trial that, if found to be effective, will assist future translation of the findings into clinical practice, relating to fidelity, reach, effectiveness, adoption, implementation and maintenance of the intervention.
3. Mechanistic aim: to investigate if the intervention improves pelvic floor muscle strength in women in the intervention arm, at 17-weeks.
4. Aim: To assess differences in the primary and secondary outcomes at 52-weeks (secondary time point) to assess any maintenance in treatment effect.
5. Aim: To assess cost effectiveness at 52-weeks if clinical effectiveness at 17-weeks is demonstrated.

6. Aim: To conduct an exploratory analysis of whether the effects of the intervention are moderated by pre-specified moderators (radiotherapy: categorical variable [yes(type)/no]; BMI: continuous variable).

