| Secondary Outcomes                                                                                                 |                                                                                                                                                                                                                                                                                                                                                                                 |                                                                                                                                                                                                                                                                          |                           |                                                                                                                          |
| International Consultation on Incontinence Questionnaire Lower Urinary Tract Symptoms Quality of Life (ICIQ-LUTSqol) [42] | 
A 20-item self-reported questionnaire capturing the impact of any type of urinary incontinence on quality of life.
 
Items are summed to create one overall score.
 
Domain-specific scores within seven domains (role limitation, physical limitations, personal relationships, emotions, sleep/energy, severity measures) will also be calculated.
           | 
Overall score ranges from 19-76. Higher scores indicating increased impact on quality of life.
 
The domain-specific scores will be calculated using a specific scoring method developed by the ICIQ group. Domain scores range from 0 (best) to 100 (worse)
 | Baseline, 17 and 52 weeks | Constrained longitudinal data analysis across all time points, accounting for stratification factor and physiotherapist. |

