|------------------------------------------------------------------------|-------------------------------------------------------------------------------------------------------------------------------------------------------------------------------------------------------------------------------------------------------------------------------------------------------------------------------------------------------------------------------------------------------------------------------------------------------------------------------------------------------------------------------------------------------------------|------------------------------------------------------------------------------------------------------------------------------------------------------------------------------------------------------------------------------------------------------------------|---------------------------|---------------------------------------------------------------------------------------------------------------------------|
| EQ-5D-5L [44, 45]                                                      | 
Health-related quality of life is self-reported via
 
 
- five dimensions: mobility, self-care, usual activities, pain/discomfort and anxiety/depression. Each dimension has 5 levels: no problems, slight problems, moderate problems, severe problems and extreme problems (descriptive component) and
 
- one additional self-rated health question scored on a visual analogue scale ranging from “the best health you can imagine” to “the worst health you can imagine” (evaluation component).
 
 | 
Ranges from -0.285 to 1.00; a negative value represents a health state that is worse than death.
 
An index score will be calculated as 1 minus the total utility captured in the EQ-5D-5L
 
The visual analogue scale score ranges from 0 -100
 | Baseline, 17 and 52 weeks | Constrained longitudinal data analysis across all time points, accounting for stratification factor and physiotherapist.  |

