| 2. Instructor qualifications  | 
Professional qualification: physiotherapist with postgraduate training in pelvic floor physiotherapy.
 
Per-protocol study training: detailed study manual and training in study processes and procedures including:
 
 
- pelvic floor muscle assessment and exercise instruction processes;
 
- instructions for teaching use of the biofeedback device;
 
- biofeedback data export;
 
- practice video-consultations to practice video-consultation skills.
 
 
During the study: regular meetings with the research team to review per-protocol procedures and discuss/address potential issues as they arise.
 |
| 3. Individual or group        | Individual physiotherapist supervised telehealth-delivered instruction in PFMT and individual home-based PFMT.                                                                                                                                                                                                                                                                                                                                                                                                                                                                                                                                                                                        |
| 4. Supervision                | Supervision will be provided remotely by a trained physiotherapist via 8 telehealth-delivered consultations, over 16 weeks. Between tele-health consultations woman will complete their PFMT unsupervised.                                                                                                                                                                                                                                                                                                                                                                                                                                                                                            |

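### Section 12.2 computes QALYs from baseline and 52 weeks only, so the 17-week utility gets no weight and the QALY gain is probably biased

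*Protocol*

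**What the plan says.** The horizon is one year. Section 12.2 of the Protocol says "Quality-adjusted life years (QALYs) gained [56] for the intervention compared to control at 52 weeks will be assessed". It then names the measurements that enter: "QALYs will be calculated based on utility scores using the EQ-5D-5L [44, 45] at baseline and 52 weeks". A parallel sentence covers the condition-specific instrument: "QALYs will also be calculated using the ICIQ-LUTSqol [42], a condition specific quality of life measure, at baseline and 52 weeks".

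The table in section 4.6 lists both the EQ-5D-5L and the ICIQ-LUTSqol at "Baseline, 17 and 52 weeks", so a 17-week value will exist for each. For the ICIQ-LUTSqol the same table gives "Overall score ranges from 19-76", plus domain scores from 0 to 100, with higher values worse on both scales.

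Two further statements fix the timing. Table 1 in section 8.2 says "Supervision will be provided remotely by a trained physiotherapist via 8 telehealth-delivered consultations, over 16 weeks". Section 3.2 sets the condition for the economic aim: "To assess cost effectiveness at 52-weeks if clinical effectiveness at 17-weeks is demonstrated".

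**The concern.** A QALY is utility accumulated over time, so it depends on the path between the end points. Two measurements a year apart impose a straight line on that path. The trial's structure gives little reason to expect one: treatment is concentrated in the first 16 weeks, the primary time-point follows at week 17, and week 52 is there to test maintenance.

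The economic evaluation is therefore triggered by an effect at week 17 and then gives week-17 utility no weight. The programme's costs are also assessed at 17 weeks, while any utility gained by then counts only through what remains at week 52. The incremental QALY and the cost per QALY, which are main results of that evaluation, are at stake.

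A lesser concern is the second QALY. A symptom-impact sum or a 0 to 100 domain score, with higher meaning worse, is not a utility anchored at death and full health. As section 4.6 scores it, the ICIQ-LUTSqol cannot supply a quality weight.

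**Working it through.** The Protocol states no QALY figure, so there is none to reproduce. The check compares the two calculations algebraically and then with illustrative values.

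**Inputs from the Protocol**
- Horizon: 52 weeks, taken as 1 year (section 12.2).
- Utilities used for QALYs: baseline and week 52 (section 12.2).
- Utilities collected: baseline, week 17 and week 52 (section 4.6).

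**Assumptions**
- Equal utility at baseline, or a difference removed by adjustment.
- Straight lines between measurements; the Protocol names no interpolation rule. Any rule that uses only the two stated visits also gives week 17 zero weight.
- d17 = 0.05, with d52 from 0 to 0.10. The Protocol gives no utility differences.

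**Formulas**, with t = 17/52 = 0.327
- Two points, as written: gain = 0.5 × d52.
- Three points: gain = 0.5 × t × d17 + 0.5 × (1 − t) × (d17 + d52) = 0.5 × d17 + 0.337 × d52.
- They agree when 0.5 × d52 = 0.5 × d17 + 0.337 × d52, that is, when d17 = 0.327 × d52: a difference growing in a straight line all year. If d17 is larger, the plan understates the gain; if smaller, it overstates it.

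**Results**

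| d17 | d52 | Two-point | Three-point | Two-point as share of three-point |
|---|---|---|---|---|
| 0.05 | 0.10 (grows) | 0.0500 | 0.0587 | 85% |
| 0.05 | 0.05 (maintained) | 0.0250 | 0.0418 | 60% |
| 0.05 | 0.02 (wanes) | 0.0100 | 0.0317 | 32% |
| 0.05 | 0 (lost) | 0 | 0.0250 | 0% |

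For a maintained effect at the same incremental cost, the cost per QALY is inflated by 0.0418/0.0250 = 1.67 times.

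The opposite direction is possible. With d17 = 0.01 and d52 = 0.05, the three-point gain is 0.005 + 0.0168 = 0.0218, against 0.0250 as written.

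**Sensitivity to visit timing.** Section 12.2 counts the 17 weeks from the start of treatment, and section 8.2 aims for the first consultation within 2 weeks of baseline. If the visit falls 19 weeks after baseline, the weight on d17 stays 0.5 and the weight on d52 becomes 0.5 × 33/52 = 0.317. The conclusion does not change.

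**The case against.** The strongest reply is that bias is not certain. The week-17 effect that the Protocol hypothesises is on the ICIQ-UI SF, not on utility, and no expected course of utility is given. Participants keep the device and may go on training (section 5.8), and the app programme has a maintenance phase (Table 1), so benefit could keep growing. This stands: the direction and size depend on the unknown utility path. It does not rescue the two-point rule, which is exact only for one path, while the data to avoid the assumption are collected anyway.

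A second reply is that such detail belongs in the SAP, which is not shown. That would hold if section 12.2 were silent, but it names the visits, twice, and leaves one out. The reply has more force for the ICIQ-LUTSqol, because an SAP could name a preference-based algorithm.

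Two stronger readings are tempting and not supported:
- A reader might infer that the 17-week EQ-5D-5L is discarded altogether. It is not: section 12.2 includes the EQ-5D-5L in the constrained longitudinal model at all three time-points. Only the QALY calculation omits week 17.
- A reader might infer the same two-point rule for costs, since section 12.2 says that "productivity lost between baseline and 52 weeks will be compared for intervention and control groups". For losses and resource use, that wording naturally describes the period over which they accrue. Nothing there excludes the 17-week cost data.

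**Conclusion.** The point holds for the QALY calculation. As written, the incremental QALY gives no weight to a utility measurement that the trial collects just after treatment ends. The result is biased unless the utility difference grows linearly over the year. If the effect is present by week 17 and maintained, the gain is understated by 40% and the cost per QALY inflated 1.67-fold. These two ratios hold for any equal d17 and d52; the absolute QALY values rest on the assumed 0.05.

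It would go too far to say that the cost-utility result will be wrong, or that the trial cannot proceed without the change. The economic evaluation is a secondary aim, conditional on 17-week effectiveness and reported separately. The primary analysis and the sample size are untouched. This should be fixed, but it is not critical to the trial.

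The ICIQ-LUTSqol is a secondary point: as scored in section 4.6 it is not a utility, and the Protocol names no conversion to one.

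**What to change.** In section 12.2, replace the two-point statement with one saying that QALYs are the area under the EQ-5D-5L utility curve through baseline, 17 and 52 weeks, using actual assessment dates, with the between-group difference adjusted for baseline utility.

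For the ICIQ-LUTSqol, either name the preference-based algorithm that turns responses into utilities, and apply the same three-visit rule, or drop that QALY and report incremental cost per point on the scale.

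The cost is two sentences in section 12.2 and matching text in the SAP, settled before unblinding. No extra visits, questionnaires or participants are needed.
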